## Abstract

**Abstract:**

**Introduction:**

Injury is a major cause of death in Rwanda, with many deaths occurring before hospital admission. Timely transport of injured patients to appropriate hospitals is crucial, ideally within an hour for severely injured patients. However, delays in reaching treatment facilities are common, with ambulance services using inefficient mobile phone communication. This project aims to evaluate the effectiveness and implementation of an innovative electronic communication platform (912Rwanda).

**Methods and analysis:**

The study will be conducted through the public ambulance service, Service d’Aide Médicale d’Urgence (SAMU), and receiving health facilities in Kigali city and Musanze district in Rwanda. The 912Rwanda intervention will be rolled out in the two locations at different times. The primary effectiveness outcome is the time from ambulance deployment to patient arrival at the health facility. Secondary effectiveness outcomes include disaggregated times of the primary outcome and clinical outcomes, such as length of stay and requirement for intensive care. These outcomes will be evaluated using an interrupted time series analysis, accounting for non-homogeneous variances, auto-regressive errors and non-linear trends where appropriate. Implementation outcomes will be evaluated using the Reach, Effectiveness, Adoption, Implementation, Maintenance (RE-AIM) Qualitative Evaluation for Systematic Translation (QuEST) framework. Cost-effectiveness will be evaluated using a cost-consequence analysis with consequences as determined by the interrupted time series analysis.

**Ethics and dissemination:**

Ethical approval was obtained from the Rwanda National Research Ethics Committee (Ref No: 99/RNEC/2023). Dissemination will occur through open-access peer-reviewed publications, relevant national and international conferences.

**Trial registration number:**

ISRCTN97674565.

STRENGTHS AND LIMITATIONS OF THIS STUDYThe use of an interrupted time series approach provides a robust quasi-experimental approach for evaluating intervention’s effectiveness when randomisation is not feasible.Implementation will be assessed using the Reach Effectiveness Adoption Implementation Maintenance (RE-AIM) Qualitative and Evaluation Study of Translation (QuEST) framework, which allows for a comprehensive understanding through both quantitative and qualitative outcomes.The cost-consequence analysis enables decision-makers to consider a range of outcomes that may be relevant to their decision-making context and to apply their own weights to these alternative outcomes, considering trade-offs between outcomes.Generalisability of findings may be limited due to variations in systems and resource availability across low- and middle-income country contexts.The rapidly evolving nature of software development and technologies may lead to research findings becoming outdated quickly, making it essential to stay updated with the latest developments.

## Introduction

 Injuries have a profoundly negative effect on both individuals and society.^1^ They cause about 4.4 million deaths globally, with tens of millions more suffering from non-fatal injuries each year.^2^ Adults of working age are primarily affected by injuries, which results in severe physical impairment, long-term disability, and psychological and economic suffering.^3^

Injuries disproportionately affect low- and middle-income countries (LMICs), where over 90% of injury-related deaths occur.^4^ In Rwanda, injuries are estimated to result in about 10% of deaths, with the majority occurring in the prehospital setting.^5^ A pillar of a good trauma service is getting injured patients to the right hospital at the right time. For severely injured patients, this should ideally be within 1–2 hours.^6 7^ Longer times are associated with increased patient mortality.^8^

As in many other LMICs, there are substantial delays in reaching hospital for injured individuals in Rwanda.^5^ Around half of injury deaths in Rwanda occur prehospital and the other half within the first 24 hours of admission.^9^ While some deaths and disability after injuries are inevitable, it is estimated that many deaths after injuries could be avoided if timely access to quality healthcare was available.^9^ In Rwanda, as in other LMICs, many avoidable deaths are due to delays in reaching the right facility in a timely manner.^10 11^

In 2007, the Rwandan Ministry of Health created a public ambulance service called the Service d’Aide Médicale d’Urgence (SAMU). This service was created to provide timely prehospital care to strengthen the health system.^12^ SAMU, originally established as an ambulance service based in the capital, Kigali, has grown to become a nationwide service covered by community-based health insurance.^13^ More than 300 ambulances are deployed, linked by a national dispatch centre, and a free emergency service number (912).^14^

Similar to other ambulance services in LMICs, all communications are made by mobile phone and very high frequency (VHF) radio.^15^ Initial explorations found that inefficient mobile phone communication and coordination between ambulance, dispatch and receiving hospitals, and lack of efficient usage of triage data from ambulance staff resulted in an average time to reach hospital of around 1 hour (figure 1, part a). One major consequence of this poor communication is that ambulance crews often lack enough information to find their patients quickly, to identify an appropriate receiving hospital for the patient or to prepare the receiving hospital in advance, wasting valuable time that could be used transporting patients to care. This represents up to 30 min of additional time from the expected journey time from injury location to hospital, with around two-fifths of trips taking longer than 1 hour.^16^ Formative work between industry, academia and policy makers led to the concept of the 912Rwanda electronic communication platform designed by the Rwanda Build Program (RWBuild), a local software company^17^ (figure 1*,* part b). The goal of the 912Rwanda platform is to reduce transport time for injured patients by connecting the patient, hospitals, ambulance crews and dispatch through the platform, reducing need for phone calls. A separate development protocol paper describes the development, training and roll-out of the 912Rwanda platform in detail.^18^ The 912Rwanda platform will be developed in multiple phases. Phase one involves the development and roll-out of software for ambulance dispatch to collect incident details, locate emergencies and enable ambulance staff to receive information. Phase two will focus on the development and integration of the destination decision support algorithm (DDSA) within the 912Rwanda platform, with additional phases launched based on local needs.

**Figure 1 F1:**
[figure not shown]
The top figure (part a) represents the current inefficient communication system, which relies on separate mobile phone and very high frequency (VHF) radio communication between the dispatch centre, ambulance crews and health facilities (without global positioning system (GPS) location), resulting in prehospital delays. The bottom figure (part b) represents the proposed 912Rwanda platform, an integrated electronic system designed to connect dispatch, ambulance crews and health facilities to reduce prehospital delays. Image created by coauthor [name] (Rwanda Build).

### Aim

The overall aim of our study is to evaluate the effectiveness and implementation of an electronic DDSA within the 912Rwanda platform, referred to as the integrated DDSA 912Rwanda platform, designed to improve prehospital transport of injured people in Rwanda. The specific objectives are as follows:

To assess the effectiveness of the integrated DDSA 912Rwanda platform in improving prehospital transport of injured people in Rwanda.To evaluate the implementation of the integrated DDSA 912Rwanda platform.To perform a cost-consequence analysis (CCA) of the integrated DDSA 912Rwanda platform compared with current practice.

## Methods and analysis

### Study design

The Rwanda912 project is a hybrid type 2 effectiveness implementation study. In summary, the effectiveness of the integrated DDSA 912Rwanda platform will be evaluated using an interrupted time series design. Implementation will be evaluated using the Reach, Effectiveness, Adoption, Implementation, Maintenance (RE-AIM) Qualitative Evaluation for Systematic Translation (QuEST) framework. Cost-effectiveness of the 912Rwanda platform will be evaluated using a CCA.

### Study setting

The study will be conducted in Kigali city and Musanze district, representing areas with predominantly urban and rural catchments, respectively. In each of these areas, the public ambulance service, SAMU, carries emergency patients to all public and private health facilities. Kigali city is the capital and largest city of Rwanda, located in the nation’s geographical centre. In contrast, Musanze district is located in the Northern Province of Rwanda, making these two areas geographically separate.

In Kigali, at the time of study development, there were 5 district hospitals, 3 referral hospitals and 37 health centres (which receive less urgent cases). In 2021/2022, half of patients were transferred to three hospitals: Kibagabaga District Hospital (21%), Nyarugenge District Hospital (16%) and Centre Hospitalier Universitaire de Kigali (13%). Over 30% of patients were either transferred to health centres or managed on-site for minor cases, with the remaining patients being transferred to other hospitals (online supplemental file 1).

In the district of Musanze, Ruhengeri Level 2 Teaching Hospital (RL2TH) serves as both the referral hospital and the only district hospital. The typically patient journey for emergencies begins at the local health centre, where patients are initially triaged and stabilised. If necessary, patients are referred to RL2TH and occasionally from there to hospitals in Kigali for further treatment. There are currently no means of prioritising patients in health centres for transfer, and 912Rwanda will be used in this case to triage patients from local health centres to RL2TH, and subsequently, to the appropriate hospital in Kigali. In Musanze, there are five available ambulances, with two typically occupied with transferring patients to Kigali and a dedicated team of seven nurses who oversee prehospital care.

### Eligibility criteria

The eligibility criteria for patient inclusion differ between the two study sites. In Kigali, all patients transferred from the incident site to a treatment facility will be included in the analysis. This encompasses transfers to both public and private health facilities within the city. In Musanze district, given that the majority of emergency patients first present to a health centre, and therefore ambulance services to pick patients up from the scene of the emergency are absent, the study will include patients transferred from health centres to the local hospital. However, patients transported from Musanze hospital to a hospital in Kigali will not be counted in the analysis.

### Intervention

The intervention, 912Rwanda, consists of an interface on mobile devices used by ambulances and hospital staff, computer interfaces for dispatch centre staff and a software platform. 912Rwanda will be developed in multiple phases. The focus of this research is on phase two; however, the effect of phase one will also be measured.

Phase one of 912Rwanda involves the development and roll-out of software only in Kigali for ambulance dispatch to collect incident details, use global positioning system (GPS) to locate and navigate to emergencies, and enable ambulance staff to receive information. It also includes an short message service (SMS) tool for communicating incident details to receiving facilities. This phase has been fully implemented in Kigali.

Phase two of 912Rwanda will focus on the development and integration of the DDSA into the software in Kigali and Musanze, the integrated DDSA 912Rwanda platform. In Musanze, a modified version of phase two of 912Rwanda will be implemented based on local needs. The DDSA will use decision algorithms to match the patient to the closest ready facility, accounting for patient medical needs and proximity. The DDSA then alerts the ambulance teams and/or dispatch of the selected facility and the rationale for this. This decision is either approved or overridden. If approved, the ambulance proceeds to the facility. If over-ridden, the ambulance team and/or dispatch (to be decided) manually enters their choice of facility and their rationale for this by means of a pre-populated survey form.

### Patient and public involvement

Extensive stakeholder and community involvement has shaped the development of this research proposal over the 2 years leading to submission. A 2-day workshop with service providers, users and other stakeholders identified improving prehospital transport for patients to appropriate facilities as a key priority. Focus group discussions with patients and community leaders identified barriers to accessing care, highlighting more efficient transport as a priority. Feedback was provided by people with lived experience (eg, patients or family members) of accessing care for injury, which was used to further refine the proposal.

To ensure ongoing community engagement throughout the project, we will establish an Injured Persons Community Group (IPCG) for Kigali and Musanze, with representation of all sections of society in this group (including those hard to reach). IPCG members will contribute to contextualising research tools, interpreting study findings through visual participatory analysis, developing and contributing to dissemination of the project results, and in policy discussions and strategy by empowering IPCG members to be involved in setting local or national agenda for improved injury care.

### Objective 1: effectiveness of intervention

#### Outcomes

The primary effectiveness outcome is the time from ambulance deployment to the patient’s arrival at a hospital (table 1). Secondary outcomes include disaggregated times of the primary outcome and the following clinical outcomes: in-hospital mortality, length of stay and requirement for intensive care.

**Table 1 T1:** Effectiveness outcomes

Outcomes	Description
Primary outcome	Time from ambulance deployment to arrival at facility
Secondary outcomes	In-hospital mortality
	Length of stay
	Requirement for intensive care
	Time from ambulance deployment to arrival at scene
	Time from arrival at scene to leaving scene
	Time from leaving scene until arriving at facility
	Time waiting to be seen after arrival at facility
Exploratory outcome	Time from dispatch call to arrival at facility*

* Only available from phase one implementation onwards.

#### Explanatory variables

The following explanatory variables will be collected: location of injured patients; facility taken to; complaint type; the Triage Early Warning score; sex; age; and presence of community-based health insurance.

#### Intervention timeline

The roll-out of the 912Rwanda intervention occurs at different times in the two study locations, as shown in figure 2. In summary, we have the following:

For Kigali city:

Baseline data: July 2022 to February 2023Phase one roll-out: March 2023 to November 2023.Phase one implemented: December 2023 to July 2025.Phase two roll-out: August 2025 to October 2025.Phase two implemented: November 2025 to June 2027.

**Figure 2 F2:**
[figure not shown]
Timeline for roll-out of 912Rwanda in Kigali and Musanze sites. Light blue represents baseline period with no intervention, grey represents roll-out periods, medium blue represents phase one implementation and dark blue represents phase two implementation (which includes phase one implementation).

For Musanze district:

Baseline data: February 2024 to February 2026.Phase two roll-out: March 2026 to July 2026.Phase two implemented: August 2026 to June 2027.

The timeline shows the staggered implementation of the intervention across the two locations, with Kigali city receiving both phases of the intervention, while Musanze district implements a modified version of phase two only.

#### Data collection

##### Time data

In Kigali, time outcome data for the baseline pre-intervention period will be collected through a time data collection app (TDCA). Time data for phase one and phase two of the intervention will be collected through the 912Rwanda platform. Data will also be collected on paper and inputted electronically as a backup throughout the study period, on which data quality checks will be performed. In Musanze, data for the baseline period will only be collected on paper and inputted electronically, while data for phase two will be collected using the 912Rwanda platform. All electronic time stamps (TDCA and 912Rwanda) are generated automatically from synchronised system clocks to ensure consistency; manual entry of time data is only used as a backup.

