### Data analysis

#### Data checking and outlier analysis

Data for the baseline will be verified against manually recorded, electronically inputted records to ensure accuracy and consistency. This process involves matching data based on incident IDs when available. If incident IDs are not available, data will be matched based on deployment time.

For each phase (baseline, phase one and phase two), minimum and maximum thresholds for the primary and secondary outcomes will be established. These thresholds will be determined based on expert opinion. This approach helps in identifying potential outliers in the dataset.

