### Strengths and limitations

The study has several strengths, including the use of interrupted time series, which provides a robust quasi-experimental approach for evaluating intervention’s effectiveness when randomisation is not feasible. The implementation of the intervention is assessed using the RE-AIM QuEST framework which allows for comprehensive understanding through both quantitative and qualitative outcomes. Additionally, the CCA will enable decision-makers to weigh the trade-offs between different costs and outcomes. However, the study also has limitations. The generalisability of findings may be challenging due to variations in contexts and resource availability across countries, potentially limiting the applicability of findings. The data collection method is different for the baseline period compared with phase one and phase two of the intervention, and different across the locations, which may lead to inconsistencies in the data. In Kigali, data are primarily collected through the TDCA app or the Rwanda912 platform, with paper forms used as a backup if electronic data capture fails, on which data quality checks will be performed. In contrast, in Musanze, data for the pre-intervention phase is collected solely on paper and inputted electronically, which presents a limitation in terms of data reliability for that phase. Furthermore, the rapidly evolving nature of software development and technologies may lead to research findings becoming outdated quickly, making it essential to stay updated with the latest developments.

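### The recording method changes between baseline and the first intervention phase, so a recording offset cannot be told apart from the Musanze phase two and Kigali phase one level shifts

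*Protocol article*

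**What the plan says.** All references are to the protocol article.

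- **Kigali, Time data.** At baseline, "time outcome data for the baseline pre-intervention period will be collected through a time data collection app (TDCA"). Afterwards, "Time data for phase one and phase two of the intervention will be collected through the 912Rwanda platform". Both electronic sources are said to stamp times automatically from synchronised clocks.
- **Musanze, Time data.** Here "data for the baseline period will only be collected on paper and inputted electronically, while data for phase two will be collected using" the platform. The same section calls manual time entry a backup only, which does not fit a site whose baseline is entirely on paper.
- **Paper records.** Within the Kigali description, Time data says: "Data will also be collected on paper and inputted electronically as a backup throughout the study period, on which data quality checks will be performed". Strengths and limitations describes Kigali collection "with paper forms used as a backup if electronic data capture fails".
- **Checking.** Data checking and outlier analysis says: "Data for the baseline will be verified against manually recorded, electronically inputted records to ensure accuracy and consistency". Matching is by incident ID or, failing that, by deployment time. Outlier thresholds are set for each phase.
- **Model.** How we will estimate these effects lists time, phase indicators (including roll-out) and their interactions. What we will estimate reports the level shift at each phase and, for Kigali, a combined effect of both phases.
- **Disclosure.** Strengths and limitations admits that the collection method differs between baseline and later phases. Of the Musanze paper baseline it says "which presents a limitation in terms of data reliability for that phase".

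**The concern.** An interrupted time series attributes to the intervention any step between the end of baseline and the start of implementation. If the instrument also changes between those two segments, a systematic difference between instruments looks the same as an effect.

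In Musanze, rounding of hand-written times or late completion of the form could produce such a step in either direction. In Kigali, what mainly remains possible is that the TDCA and the platform mark deployment or arrival at a different event.

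The Musanze phase two shift is that site's only intervention level effect. Phase two is also the stated focus of the research (Intervention section). A spurious step there could create or hide a benefit on the primary outcome, and a longer series would not reduce it.

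**Working it through.** **Inputs**
- Weeks, from Sample size calculation: Kigali 31 / 87 / 87; Musanze 104 / 48.
- Roll-out gaps, from the dates in Intervention timeline: Kigali March to November 2023 (about 39 weeks) and August to October 2025 (about 13 weeks); Musanze March to July 2026 (about 22 weeks).
- Example, from Sample size calculation: SD 30 min, standardised effect 0.5, hence 0.5 × 30 = 15 min, which reproduces the stated figure.
- Assumed: a 5 min offset, constant over time; AR(1) correlation 0.3; two-sided 5% test.

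**Step 1. Can the model separate the offset?**
Musanze model: mean = b0 + b1·time + b2·post + b3·post·(time since start). An instrument indicator is 0 on paper and 1 on the platform, so it is the same column as *post*. The design then has 5 columns and rank 4.

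Kigali model: intercept, time, and a level and a trend term for each phase, which is 6 columns. The instrument indicator equals the phase one level term (1 from phase one onwards), giving 7 columns and rank 6. In both sites the offset is completely confounded with the first level shift.

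**Step 2. Where does a constant offset go?**
Projecting a 5 min offset onto the coefficients by generalised least squares gives:

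| Coefficient | Bias (min) |
|---|---|
| Musanze phase two level | +5.0 |
| Musanze trend change | 0.0 |
| Kigali phase one level | +5.0 |
| Kigali phase two level | 0.0 |
| Kigali trend terms | 0.0 |

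The Kigali combined effect is a linear combination that includes the phase one level shift, so it carries the same 5 min. These values do not depend on the SD or the autocorrelation.

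**Step 3. Size**
Against the example effect, 5/15 = 33%; an offset of 15 min would equal all of it. Against the quoted SD, 5/30 = 0.17 SD.

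The chance that the offset alone gives a significant level shift is Φ(5/SE − 1.96) + Φ(−5/SE − 1.96). At AR(1) = 0.3, the SE of the level shift is 0.518 × SD in Musanze and 1.493 × SD for Kigali phase one.

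| SD of weekly means (min) | Musanze SE | Musanze chance | Kigali phase one SE | Kigali phase one chance |
|---|---|---|---|---|
| 30 (the document's example) | 15.5 | 6% | 44.8 | 5% |
| 10 (assumed) | 5.2 | 16% | 14.9 | 6% |
| 4.2 (assumed: 30/√50) | 2.2 | 62% | 6.3 | 12% |

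The last row treats 30 min as a per-trip SD, whereas the protocol describes it as an SD across weekly periods. The test result depends strongly on this choice; the bias is 5 min in every row.

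**Step 4. Would a parallel paper record help?**
With a paper series stacked beside the electronic one, the Kigali design has 8 columns and rank 8 if paper covers all weeks. Musanze has 5 columns and rank 5, but only if paper continues after launch. The offset can then be estimated. Time data does not clearly say that paper continues in Musanze.

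**The case against.** **What stands against the point.** The protocol is open about the change. Kigali's two electronic sources share automatic, synchronised stamps, so rounding and late write-up do not apply to them, and nothing says that their event triggers differ. Checking is not confined to baseline: quality checks on paper records and phase-specific outlier thresholds are also planned, although neither removes an offset. Roll-out periods separate the segments, so the switch is not literally at a single date. The instrument used in roll-out is not stated and no overlap is described, so the comparison of baseline with implementation is still exposed. An offset sensitivity analysis could sit in an unseen statistical analysis plan. That answers the analysis part only, because paper that was never recorded cannot be recovered by later analysis.

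**Stronger readings that the document does not support.**
- A reader might infer that the results of both sites are wholly compromised. Kigali's phase two shift has the platform on both sides and carries no such bias.
- A reader might infer that the Musanze phase two series will drop trips not logged on the platform while baseline holds every trip. Table 2 anticipates incomplete platform data, but no section says that such trips are excluded; backup entry and missing outcome data are both mentioned.
- A reader might infer a flat contradiction about Kigali paper. Paper kept throughout, and drawn on when capture fails, could be one arrangement. It is an ambiguity, but one that decides whether a bridging series exists.
- A reader might infer that an offset of a few minutes exceeds the detectable effect. That needs both an offset the document does not give and a per-trip reading of its SD.

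**Conclusion.** The point holds for three estimates: the Musanze phase two level shift, the Kigali phase one level shift and the Kigali combined effect. Each absorbs the whole of any constant recording offset, and the analysis as described neither estimates nor removes it. The concern is most serious in Musanze, where manual and automatic times are compared, and milder in Kigali. It does not extend to the Kigali phase two level shift or, for a constant offset, to any trend change.

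The size is unknown; 5 min, or one third of the example effect, is only an illustration. The one-for-one result assumes an offset that is constant over time and an analysis in minutes. An offset that drifts, or a log-scale analysis, could also affect the trends.

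**What to change.** 1. **Musanze:** continue the existing paper form alongside the platform through roll-out and phase two, for all trips or for fixed sample weeks. Staff should complete it without copying platform times, or the paired differences will understate the offset.
2. **Kigali:** reconcile Time data with Strengths and limitations on whether paper is kept for every trip throughout or only when electronic capture fails. The baseline is dated 2022 to 2023, so only paper that already exists can serve for that period.
3. **Checking:** extend the matching of paper and electronic records in Data checking and outlier analysis to phases one and two.
4. **Analysis:** prespecify a paired-trip estimate of the offset. Add an offset-corrected or paper-to-paper interrupted time series as a sensitivity analysis for the three exposed effects, using paper times for trips with no platform record.

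Platform times can stay primary. Making noisier paper times the primary Musanze series is a debatable trade and is not needed to remove the problem.

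**Cost:** duplicate recording in Musanze for up to about 16 months (5 of roll-out plus 11 of phase two), less with sample weeks, on a form already in use; the record matching at both sites; and extra model runs. Paper times will be noisier in the sensitivity analysis. The Musanze step is the urgent one, because it depends on records being made at the time.
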